## Abstract

The mental health of people living in farming communities has been identified as an important public health issue. Cumulative exposure to a range of situational factors contributes to heightened risk of poor mental health and suicide. Access to evidence-based psychological treatments is limited by the availability of skilled mental health professionals. The aim of this trial—co-designed by members of the farming community—is to establish the feasibility of conducting randomised controlled, trial-testing, peer-worker-delivered Behavioural Activation in the farming community. We will undertake a single-blind, parallel group, randomised controlled feasibility trial in rural Australia. People living in farming communities aged over 15 years and experiencing moderate to moderately severe depression symptoms will be included in the trial. Participants will be randomly allocated on a 1:1 ratio to 10 sessions of peer-worker-delivered behavioural activation (Back-on-Track) or a self-help workbook (Managing Stress on the Farm). Peer workers are members of the farming community that have completed training in behavioural activation and demonstrated competence. Feasibility outcomes include establishing recruitment rates, willingness to be randomised, dropout rate from trial, acceptability of peer delivered behavioural activation, and willingness to complete trial measures. The trial will contribute high quality evidence of the feasibility of undertaking a full-scale, randomised controlled trial of peer-delivered Behavioural Activation in farming communities in rural Australia.

## 1. Background and Rationale

Suicide risk in farming populations is up to twice that of the general Australian population [1,2,3]. Although higher rates of diagnosed mental illness have not been clearly identified in this population [4], the association between mood and suicidal thinking seems to differ between members of the farming community and the general population. There is strong evidence for a range of situational factors (influenced by the farming context) that negatively influence farmer mental health and suicide risk [5,6,7,8,9,10].

There is some evidence that farmers are generous at providing help to others but are reluctant to ask for help themselves [11]. Most farmers live in communities in which accessing specialist mental health services is challenging [12]. Where support is available, health services and health care workers may not understand the realities of life and work in the farming environment [13]. The unique barriers to support seeking identified in farming communities may deter people from seeking help for mood problems, particularly when they have had previous negative experiences [14]. However, finding health care professionals with an understanding of farming practices and community values has been identified as an important facilitator to help seeking by Hull et al. [15].

There is sound evidence from systematic reviews of randomised controlled trials that Behavioural Activation is a safe and effective treatment for depression—a predictor of suicide [16,17]. A Cochrane review included 53 studies involving 5495 participants and concluded that there was evidence of moderate certainty that Behavioural Activation was more effective than treatment as usual [17].

Behavioural Activation is a brief psychological treatment focused on increasing behaviours that enhance mood and reducing avoidance behaviours (e.g., sitting alone and ruminating) that negatively impact mood. Unlike Cognitive Behavioural Therapy (CBT), workers without specialist mental health training can learn to deliver Behavioural Activation with minimal (typically described as around 5 days) training and ongoing supervision and support [16]. Consequently, Behavioural Activation could be delivered at-scale to people experiencing depression or low mood in communities where access to specialist mental health services is limited, such as farming communities in rural Australia.

There is growing evidence that peer-delivered mental health care services reduce relapse and rehospitalisation, and improve empowerment, hope, self-efficacy, engagement, and recovery [18]. Working with members of the farming community to deliver Behavioural Activation to their peers (enabling the shared context, characteristics, and cultural awareness to ‘walk in their shoes’) has the potential to overcome many well-established barriers to mental health help seeking and improve outcomes for this at-risk group [19].

### 1.1. Objectives

The objectives of this feasibility trial address (i) the recruitment, training, and retention of peer workers, (ii) the recruitment, randomisation, and completion of intervention and outcome measures by members of the farming community with depression, and (iii) fidelity of intervention delivery. Trial feasibility will be established if the following outcomes are met:Peer workers-Ten peer workers are recruited to participate in the trial.-Eight peer workers successfully complete the Behavioural Activation training package.-Six peer workers deliver the Back-on-Track intervention to at least one participant.-Five peer workers are retained through to the completion of the trial.-Peer workers attend at least eight of the 13 group supervision sessions.Members of the farming community with depression (participants)-Approximately 200 indicated that they are interested in taking part in the research.-Forty participants meet eligibility criteria and consent to participate in the trial.-Forty participants complete baseline (week 0) measures.-Forty participants agree to be randomised.-Forty participants start the trial.-Sixteen participants complete the experimental intervention (defined as attending at least six of the 10 Behavioural Activation sessions). Note: there is no feasibility measure for level of completion for the control group given provision of treatment as usual (Managing Stress on the Farm).-Thirty-two participants complete week 10 measures.-Twenty-eight participants complete week 26 measures.Ninety percent of the Behavioural Activation sessions are delivered to an at least satisfactory level of fidelity to model (independently determined using the Behavioural Activation fidelity assessment) [20].

The trial is not powered or designed to detect statistical between-groups differences in primary or secondary outcomes, and no statistical analysis will be undertaken or reported.

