### 2.11. Sample Size

The intended sample size is 40 participants (approximately 20 in the intervention supported by 10 peer workers and 20 in the control groups). Sample size calculations are not appropriate for feasibility trials, and a sample of 40 is generally considered adequate to establish that a definitive trial is feasible [29].

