### 2.12. Recruitment

#### 2.12.1. Procedures for Recruiting People with Depression

Based on figures provided by Agriculture Victoria, we estimate that 69,000 people are employed in agricultural production in Victoria. Trials of Behavioural Activation are typically able to recruit around one in three people that are asked to participate [30]. We anticipate that around a third of people (approximately 23,000) in the farming community will meet our inclusion criteria and predict that around 200 potential participants will express an interest in participating in the trial. Recruitment will be monitored at our weekly trial management groups and, if fewer people than expected indicate interest, we will revise our recruitment strategy in consultation with our Community Reference Group.

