#### 2.12.3. Pre-Screening and Consent Procedures

Members of the farming community interested in participating in the trial will be asked to submit an expression of interest by telephone, email, or online. The researcher will contact potential participants by phone to discuss the trial in detail and to obtain verbal consent to complete screening. At the start of the screening interview, participants will be asked to complete the PHQ-9. Researchers will total the score and feedback to participants.

PHQ-9 cut-off scores from Kroenke et al. [24] will be used. Potential participants scoring below five or over 19 on the PHQ-9 will be notified that they do not meet trial inclusion criteria and are not eligible to take part in the trial. Ineligible participants will be sent a copy of the Managing Stress on the Farm self-help workbook. Ineligible participants scoring over 19 (indicative of severe depression) will be informed by the researcher that their score suggests that they may be experiencing severe depression and will be asked if they are currently receiving any psychological or pharmacological treatment for their mental ill-health. If they are, the researcher will advise the individual to contact their mental health clinician as soon as possible. In instances where the individual does not have a mental health clinician, they will be advised to contact a health professional. The researcher will explain that, due to the severity of their psychological symptoms, they do not meet trial inclusion criteria.

Potential participants that meet trial inclusion criteria will be given a detailed verbal explanation of the trial procedures and informed that they will receive an email containing a written Participant Information and Consent Form (PICF) to review and sign. If they are unable to receive the PICF via email, a paper copy will be mailed to them. If no signed PICF (electronic or paper copy) is received after 7 days, the potential participant will be followed up by phone, asking if they still wish to take part in the research.

During the consent process, participants will be informed that the information they provide will be kept strictly confidential except in circumstances where they indicate that they may harm themselves or other people. The risk of harm to self will be determined from discussion with participants.

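### About 200 expressions of interest is a pass condition for feasibility, so read literally the rule fails a trial that fills its forty places from clearly fewer contacts

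*Protocol article*

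**What the plan says.** Section 1.1 introduces its list with "Trial feasibility will be established if the following outcomes are met". Among the participant items are "Approximately 200 indicated that they are interested in taking part in the research" and, separately, "Forty participants meet eligibility criteria and consent to participate in the trial". Nothing there says that meeting the second makes the first redundant. Section 2.11 sets the target: "The intended sample size is 40 participants".

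The support for the 200 is in section 2.12.1, which makes three statements in turn:

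- "Trials of Behavioural Activation are typically able to recruit around one in three people that are asked to participate"
- "We anticipate that around a third of people (approximately 23,000) in the farming community will meet our inclusion criteria"
- the authors then "predict that around 200 potential participants will express an interest in participating in the trial"

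No step links the third statement to the first two. Section 2.12.3 gives the order of events: a person expresses interest, is phoned, completes the PHQ-9, and only then "Potential participants that meet trial inclusion criteria will be given a detailed verbal explanation of the trial procedures".

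**The concern.** There are two problems, and the first needs no assumption about recruitment rates.

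**Direction of the criterion.** Interest is the input to recruitment and enrolment is the output. With the output fixed at forty, fewer expressions of interest mean better conversion. A floor on the input, applied as well as the enrolment target, penalises good conversion. A trial that filled forty places from 120 to 150 contacts would miss a listed condition, while one that needed 200 or more would meet it.

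**Basis of the figure.** The pair of 200 and forty implies that one interested person in five enrols. The only rate cited in section 2.12.1 is one in three, and it is attached to a different group (people asked to participate). The protocol does not say what share of interested people it expects to be eligible, so the reader cannot get from the cited rate to the 200.

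At stake is the feasibility verdict itself, and the yield that a definitive trial would need for planning. Participant safety and data collection are not affected.

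**Working it through.** **Inputs**

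- Interest criterion: about 200 (section 1.1); the same figure is forecast in section 2.12.1.
- Enrolment criterion and sample size: 40 (sections 1.1 and 2.11).
- Cited recruitment rate: 1/3 of people asked to participate (section 2.12.1).
- Eligible share of the farming community: 1/3 (section 2.12.1).
- Eligible share among people who express interest, *e*: not given. It is treated as an assumption and varied.

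**Step 1. The protocol's own figures.** 69,000 / 3 = 23,000, which reproduces the stated number of eligible people. The 200 cannot be reproduced, because no derivation is given. The implied yield is 40 / 200 = 20%.

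**Step 2. Link between the cited rate and the 200.** If one in three applies to eligible people who are asked:

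contacts needed = 40 / (*e* × 1/3) = 120 / *e*; enrolled from 200 = 200 × *e* / 3

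| *e* (assumed) | Contacts needed for 40 | Enrolled from 200 |
|---|---|---|
| 1 | 120 | 66.7 |
| 0.8 | 150 | 53.3 |
| 0.6 | 200 | 40.0 |
| 0.5 | 240 | 33.3 |

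The row *e* = 1 is the same as applying one in three directly to everyone interested. The figures 200 and 40 agree only at *e* = 0.60.

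**Step 3. How often the line would be missed.** Assume independent contacts, a constant yield *p* from interest to enrolment, and counting of contacts that stops at the 40th enrolment. Let *N* be the number of contacts needed. Then *N* ≥ *t* exactly when the first *t* − 1 contacts give at most 39 enrolments:

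P(*N* ≥ *t*) = P(Binomial(*t* − 1, *p*) ≤ 39)

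The protocol does not define approximately 200. The main reading here is at least 160; a strict 200 is shown beside it.

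| Yield *p* | P(*N* ≥ 160) | Missed at 160 | P(*N* ≥ 200) | Missed at a strict 200 |
|---|---|---|---|---|
| 20% (implied by section 1.1) | 0.934 | 7% | 0.486 | 51% |
| 25% | 0.488 | 51% | 0.044 | 96% |
| 1/3 | 0.010 | 99% | 0.00001 | over 99.9% |

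At a yield of 1/3 the median number of contacts needed is 119. The chance of missing the line rises with the yield, which confirms the direction of the problem.

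The result is sensitive to the cut-off. At a 25% yield, lowering it from 160 to 140 raises the chance of meeting the line from 49% to 82%.

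**Step 4. Precision of the yield.** For 40 of 200, the 95% Wilson interval is 15.0% to 26.1%.

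**The case against.** The strongest reply is that the protocol forecasts about 200 expressions of interest, so a trial that goes as forecast meets the criterion. This stands. A reader might infer that a trial recruiting as the protocol expects would fail its own rule; section 2.12.1 contradicts that inference. At the implied 20% yield, with 160 accepted as approximately 200, the line is met about 93% of the time.

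A reader might also infer that 120 is the protocol's own requirement and the 200 a miscalculation. The documents do not support this either. The one in three refers to people asked to participate, whereas section 2.12.3 places screening after the expression of interest, and sections 2.5.1 and 2.5.2 list several grounds for exclusion. The 120 holds only if screening loses nobody, or if that loss is already inside the cited rate; the article says neither. Nor should the one third eligible be carried over to volunteers to give one in nine, since section 2.12.1 states it for the farming community as a whole.

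It can further be argued that reach is a legitimate feasibility outcome in a population reluctant to seek help (section 1), and that section 2.12.2 wants the number of contacts in order to plan the definitive trial. That is a good reason to count and report contacts. It does not justify failing a trial that has already enrolled forty.

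Finally, the abstract lists recruitment rates as an outcome and section 3.3 promises numbers and proportions, so the yield could be calculated anyway. This is true, but it does not change the verdict rule in section 1.1. The protocol also does not say that interest stops being counted at the 40th enrolment. If counting continued, the chances of missing the line would be lower than in the working.

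**Conclusion.** The point holds as a defect in the decision rule. Section 1.1 makes a volume count a separate condition of feasibility, and read literally it works against a trial that converts interest into enrolment efficiently. This follows from the wording alone.

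The second part is narrower: 200 and the one-in-three rate are unreconciled but not incompatible. They agree at 60% eligibility among interested people, a share the protocol leaves unstated. No arithmetic error is shown.

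The size depends on the true yield and on what counts as approximately 200. With a cut-off of 160, independent contacts and a stop at forty, the line is missed about 7%, 51% and 99% of the time at yields of 20%, 25% and one in three. Both the cut-off and the 25% yield are assumptions made for this check. The one in three is the cited rate applied to all interested people, the most favourable reading of it. The change should be made, since the rule can turn a successful recruitment into a failed verdict.

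**What to change.** 1. In section 1.1, remove the 200 line as a pass condition. Alternatively, keep it and add that reaching forty from fewer contacts does not fail the verdict.
2. Report expressions of interest as a descriptive count. Report the yield, participants randomised divided by people expressing interest, with a 95% interval (for 40/200, Wilson 15% to 26%).
3. In section 2.12.1, state separately the assumed eligible share among interested people and the assumed uptake among eligible people, and show how they lead to the forecast. If 200 is kept as the forecast with one-in-three uptake, the implied share is 60% and should be labelled as an assumption.
4. Do not replace 200 with 120. That would assume no screening loss beyond the cited rate, and it would keep the floor.

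The cost is protocol wording only. The volume target is lost as a criterion (or no longer decides the verdict if forty are enrolled), but the count is still collected, reported and available for planning the definitive trial.

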### 2.13. Allocation

Randomisation will be undertaken using an online randomisation service—Sealed Envelope Ltd London, UK [34]—and managed by the La Trobe University Clinical Trials Platform to ensure the research team remain blinded to group allocation. Randomisation will be by random permuted blocks with a 1:1 ratio.

The Clinical Trials Platform will contact the peer worker by phone and inform them of the allocation of a new trial participant and ask if there is any known conflict of interest with the allocated participant. If there is no conflict of interest, the peer worker will be provided with allocated participant details (name, telephone number, and email address) and will call the participant to introduce themselves and arrange the first session.

If there is a conflict of interest identified (either by the peer worker or participant), the participant will be reallocated to a different peer worker. Participants allocated to the control group will be contacted by phone by the Clinical Trials Platform to inform them of the allocation, emailed an electronic copy, and sent a hard copy of the Managing Stress on the Farm workbook in the post.

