### 2.14. Blinding (Masking)

This is a single-blind trial. All research team members will be masked to group allocation with the exception of the Clinical Trials Platform team, who will need visibility of allocation to provide contact details to peer workers and mail resources to participants in the control group. Peer workers will be delivering the intervention and as such will not be masked.

As part of the consent process, a full explanation of the trial design will be given to participants including a description of the Back-on-Track (experimental) and Managing Stress on the Farm self-help workbook (control) interventions. Consequently, participants will not be blind to group allocation (an open-label trial). Awareness of group allocation can impact how participants respond to the intervention they receive. Participants who know they have been allocated to Back-on-Track may have more favourable expectations than those allocated to the Managing Stress on the Farm group, who may feel disappointed. Participants in the trial may assume that Back-on-Track will be better than Managing Stress on the Farm. Telling participants which intervention they will receive may also influence how participants complete outcome assessments. It is also possible that knowledge of treatment allocation may also impact participant compliance and dropout from the study. It will be important when interpreting the outcomes of this feasibility trial to acknowledge the context within which the research was conducted.

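### The two retention criteria are pooled over arms, so the feasibility verdict is insensitive to attrition that differs between arms

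*Protocol article*

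**What the plan says.** Section 1.1 (Objectives) states the decision rule: "Trial feasibility will be established if the following outcomes are met". Among the outcomes listed are these two: "Thirty-two participants complete week 10 measures.-Twenty-eight participants complete week 26 measures". Both are totals over all participants.

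Section 2.11 gives the arm sizes: "The intended sample size is 40 participants (approximately 20 in the intervention supported by 10 peer workers and 20 in the control groups". Section 2.13 adds: "Randomisation will be by random permuted blocks with a 1:1 ratio".

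Only one participant criterion in section 1.1 is specific to an arm: 16 people must attend at least six of the ten Behavioural Activation sessions. It counts attendance, not completed outcome measures, and concerns the experimental arm. The same section says that no completion measure is set for the control group.

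Section 2.14 (Blinding) acknowledges that participants know their allocation. It refers to "those allocated to the Managing Stress on the Farm group, who may feel disappointed" and goes on: "It is also possible that knowledge of treatment allocation may also impact participant compliance and dropout from the study". Its response is to ask that the context be acknowledged when the outcomes are interpreted.

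**The concern.** The trial is meant to show whether a definitive two-arm randomised trial can be run, with change in PHQ-9 as its primary outcome. Loss to follow-up that differs between arms would threaten that comparison more than the same loss spread evenly. The setting makes a difference plausible: allocation is open, one arm has ten personal sessions, and the other has a workbook with automated weekly mood prompts.

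A pooled count lets good retention in one arm offset poor retention in the other. The pre-stated verdict could therefore be positive while control-arm follow-up was too weak to carry into a definitive trial. The concern is with the threshold that section 1.1 fixes, not with whether counts by arm will be shown descriptively.

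**Working it through.** **Inputs from the protocol.** Week 10 threshold: 32 of 40 = 80%. Week 26 threshold: 28 of 40 = 70%. Arms: about 20 and 20. The protocol derives these thresholds from no calculation, so there is no figure to reproduce beyond the two percentages.

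**Step 1: largest one-arm loss that still passes.** The fewest retained in one arm is the threshold minus the size of the other arm.

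| Visit | Fewest retained | Largest loss |
|---|---|---|
| Week 10 | 32 − 20 = 12 of 20 | 8 of 20 = 40% |
| Week 26 | 28 − 20 = 8 of 20 | 12 of 20 = 60% |

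At week 26, the only passing splits that leave an arm below 10 of 20 are 20+8, 20+9 and 19+9. At week 10 there are none. Milder imbalance also passes at week 26, for example 18 + 10 = 28 (90% against 50%). Because the arms are only approximately 20, a 21/19 split would let the smaller arm fall to 28 − 21 = 7 of 19, a loss of 12/19 = 63%.

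**Step 2: do the other criteria block this?** Take the experimental arm at 20/20 at both visits, and the control arm at 12/20 at week 10 and 8/20 at week 26. The totals are 32 and 28. The requirement for 16 session completers can also be met. The remaining criteria concern recruitment, baseline, randomisation, starting the trial, peer workers and fidelity, and none bears on control-arm follow-up. Every listed criterion can therefore be met.

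**Step 3: chance of passing under assumed true retention.** Let A ~ Bin(20, p₁) and B ~ Bin(20, p₂) be independent. The pooled rule at week 26 passes with probability P(A + B ≥ 28), the sum of P(A = a)·P(B = b) over all a + b ≥ 28. With the floor, the sum is restricted to a ≥ 12 and b ≥ 12. The rates p₁ and p₂ are assumptions; the protocol gives none by arm.

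| Assumed week 26 retention | Mean | Pooled rule | Pooled rule plus 12/20 floor |
|---|---|---|---|
| 70% / 70% | 70% | 0.577 | 0.561 |
| 90% / 50% | 70% | 0.581 | 0.246 |
| 95% / 50% | 72.5% | 0.733 | 0.251 |
| 80% / 80% | 80% | 0.957 | 0.950 |

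The first two rows have the same mean, and the pooled rule treats them alike.

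**Step 4: the same at week 10**, with P(A + B ≥ 32) and an example floor of 14 of 20 in each arm. At 80%/80% the probability goes from 0.593 to 0.585. At 95%/65%, which has the same 80% mean, it goes from 0.595 to 0.401.

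**Step 5: how sharp is a floor on 20 people?** For a single arm, P(B ≥ 12) is 0.887 at 70% true retention, 0.252 at 50% and 0.057 at 40%. Both arms at 70% clear it with probability 0.887² = 0.79.

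**The case against.** Pooled retention targets are a design choice in a descriptive feasibility trial and contradict nothing in the protocol. Differential dropout would probably be noticed: section 3.3 promises numbers and proportions, section 4.1.1 interviews five participants from each group, the post-trial survey goes to both arms, and the control arm has weekly contact. The session-attendance criterion also indirectly limits loss from the experimental arm. All of this stands, but none of it is a threshold. Section 1.1 says what establishes feasibility, and that rule does not respond to imbalance.

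Three stronger readings are tempting, and the documents do not support them.

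- A reader might infer that both criteria can be met with most of an arm gone. This is true only at week 26, and only if the other arm keeps 19 or 20 of 20. Even at assumed rates of 95%/50%, passing week 26 with the weaker arm below 10 of 20 has probability about 0.16.
- A reader might take section 2.14 to predict heavy control-arm loss. It says only that dropout may be affected. It gives no size and does not tie dropout to one arm.
- A reader might compare 0.733 at 95%/50% with 0.577 at 70%/70% and conclude that the rule rewards imbalance. Most of that gap comes from the higher mean: with both arms at 72.5% the rule passes with probability 0.71. The rule is indifferent to imbalance; it does not favour it.

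Any particular floor is also a judgement, since the protocol supplies no basis for one, and with 20 per arm it will misclassify some trials.

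**Conclusion.** The point holds as a weakness of the decision rule. Every listed criterion can be met with one arm, in practice the control arm, having lost up to 40% by week 10 and up to 60% by week 26. Those bounds are arithmetic on the protocol's own figures, assuming 20 per arm, and are extremes that need full retention in the other arm. The wider finding is the insensitivity: at an assumed 70% mean, the week 26 rule passes about 58% of the time whether or not the arms differ by 40 percentage points. The probabilities rest on assumed rates and independent binomial counts; the bounds do not. The rule should be changed, because the change is cheap and section 2.14 already names the risk.

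**What to change.** In section 1.1, keep the two pooled totals and add a floor that each randomised arm must meet, set somewhat below the pooled rate. Example values are at least 14 of 20 (70%) at week 10 and at least 12 of 20 (60%) at week 26, scaled to the actual arm sizes. State that if either arm falls below its floor, feasibility is not claimed without a revised retention plan for the definitive trial.

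Applying the full pooled percentages within each arm (16 and 14 of 20) would be stricter than needed: at 70%/70%, both arms reach 14 of 20 at week 26 with probability only 0.37.

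The cost is a wording change, with no new data or participants. The verdict becomes slightly harder to reach. The floor is also imprecise: an arm with true retention of 50% still clears 12 of 20 about 25% of the time, so it should be read as a guard against gross imbalance and not as a test of equal retention.
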